   5. SUBDJECTS [IDENTIFICATION 10](#_TOC_250009)
   6. SOURCES OF PERSONNAL DATAS 10
   7. POPULATION STUDIED. 10
   8. CONDUCT OF THE RESEARCH 10
2. [DATA MANAGEMENT. 11](#_TOC_250008)
   1. METHOD OF DATA COLLECTION 1l
   2. DATA CIRCUIT, PROTECTION AND CONFIDENTIALITY. 1 l
   3. DOCUMENTS AND DATA RETENTION. 1 l
3. [STATISTICAL ASPECTS. 12](#_TOC_250007)
   1. STATISTICAL JUSTIFICATION OF SAMPLE SIZE 12
   2. DESCRIPTION OF STATISTICAL METHODS 12
4. [ETHICAL AND LEGACY ASPECTS. 12](#_TOC_250006)
   1. ROLE OF THE SPONSOR. 12
   2. METHODS OF INFORMING THE RELEVANT POPULATION. 12
   3. PROCEDURES FOR COMPUTER REGULATION AND FREEDOM 13
   4. REQUEST FOR OPINION OF THE ETHICS COMMITTEE 13
   5. RESPONSIBILITY OF THE INVESTIGATOR TOWARDS THE SPONSOR. 13
   6. [FINAL REPORT 13](#_TOC_250005)
5. [RULES CONCERNING PUBLICATION 13](#_TOC_250004)
   1. [MENTION OF CHSF AFFILIATION FOR PROJECTS PROMOTED BY CHSF 13](#_TOC_250003)
   2. MENTION OF CHSF SPONSOR IN THE MANUSCRIPT ACKNOWLEDGMENTS. 13
6. **RESUME**

| **Full title** | Study of post-healing follow-up in people in remission of a diabetic foot wound | | |
| --- | --- | --- | --- |
| **Acronym** | Pied-REM | | |
| **Investigator coordonnator** | [name]  Endocrinology,Diabetology and Metabolic Diseases Unit  Centre hospitalier Sud Francilien [name]  Tél : [name]  Mail : [[contact]](mailto:[contact]) |  |  |
| **Scientific Director** | [name] [name]  Endocrinology,Diabetology and Metabolic Diseases Unit  Centre hospitalier Sud Francilien [name]  Tél : [name]  Mail : [contact] |  |  |
| **Sponsor** | Centre Hospitalier Sud Francilien | | |
| **Scientific justification** | The rate of recurrence of diabetic foot wounds is 60% at 3 years. We would like to examine the link between post-healing follow-up and recurrence. | | |
| **Objectiv and primary outcome** | Primary objectiv : Evaluate the benefit of a specific multidisciplinary follow-up of the healed diabetic foot at the rate of 2 annual consultations on wound recurrence.  Primary outcome: Foot wound recurrence at 2 years | | |
| **Objectives and secondary outcomes** | Secondary objectives :  Evaluate the benefit of a specific multidisciplinary follow-up of the healed diabetic foot at the rate of 2 annual consultations on :   - recurrence with the need for hospitalization. - pedicure follow-uo of patients. - wearing suitable footwear.   Secondary outcomes   - Hospitalization for foot wound at 2 years - Pedicure follow-up at 2 years - Wearing suitable footwear at 2 years | | |
| **Type of study** | Monocentric retrospective cohort study  observational study. | | |

| **Inclusion criteria** | - Patient with a type 1 or 2 follow-up at the Centre Hospitalier Sud-FranciIien (CHSF), - Discharge from hospital from a foot wound between 2017 and 2019 with a 2 years post-healing follow-up - Age greater than or equal to 18 years, - People not deprived of liberty, - Subject informed of the study and did not object. |
| --- | --- |
| **Non-inclusion criteria** | Patient refusing the study. |
| **Information for participants** | Individual patient information |
| **Number of subjects**  **Selected** | 158 patients |
| Number of centers | see addenda n°1 |
| Duration of the research | Period of time for which data is available : 2017-2021 Duration of the research: 1 year |

#### 1.Expected outcomes and opportunities / Hypothèses/ Justification of public interest

We hypothesize that 2 annual multidisciplinary consultations in diabetic patients with a healed foot ulcer ensure optimal follow-up and minimize the risk of recurrence and hospitalization. In our experience, such a follow-up limits the rate of recurrence at 1 year to about 25%, compared to 40% of recurrence of diabetic foot ulcers with a conventional follow-up. Such a result would have a definite benefit in terms of health care expenses (treatments, hospitalization, work stoppages).

#### OBJECTIVES

- 1. **Primary objectiv**

To evaluate the benefit of a specific multidisciplinary follow-up of the healed diabetic foot at the rate of 2 annual consultations on wound recurrence.

#### Secondary objectives

Evaluate the benefit of a specific multidisciplinary follow-up of the healed diabetic foot at the rate of 2 annual consultations on :

- recurrence with the need for hospitalization.
- pedicure follow-uo of patients.
- wearing suitable footwear.

#### METHOD ET POPULATION

- 1. **Outcomes**

#### Primary outcome

Foot wound recurrence at 2 years

#### Secondary outcomes

- Hospitalization for foot wound at 2 years
- Pedicure follow-up at 2 years
- Wearing suitable footwear at 2 years
  1. Type of study

Monocentric retrospective cohort study, observational study.

9/î4

###### Duration of the research

Period of time for which data is available : 2017-2021

Duration of the research: 1 year

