###### Study population

- - 1. **Inclusion criteria**
- Patient with a type 1 or 2 follow-up at the Centre Hospitalier Sud-FranciIien (CHSF),
- Discharge from hospital from a foot wound between 2017 and 2019 with a 2 years post-healing follow-up
- Age greater than or equal to 18 years,
- People not deprived of liberty,
- Subject informed of the study and did not object.

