###### Conduct of the research

Eligible patients are selected from the computerized database of the diabetes department of the CHSF, over the period 2017-2019. Eligibility criteria are then verified in the patient record.

After sending the information form to the patients and respecting the no-objection period, the patients will be included in the study and the data collection will be performed.

The data are collected from the patient records, and are recorded on a computer medium.

Each patient will be assigned a group, either the experimental group or the control group. The 2 groups will be defined according to the number of consultations honored each year over a 2-year period Patients who have honored at least an average of 2 consultations per year for 2 years, i.e. 4 sessions over 2 years at least, will be included in the experimental groupPatients who do not reach this number will be included in the control group.

t0/14

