###### Nature of data collected

- Verification of inclusion criteria

- Age and gender

- Type and duration of diabetes

- Presence of arterial disease, diabetic neuropathy

- History of amputation

- HbAlC

During the 2-year observation period from the date of recovery:

- Number of follow-up visits honored over a two-year period from the time of healing

- Recurrence of foot wounds Hospitalization for foot wounds

- Pedicure follow-up

- Appropriate footwear.

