###### Description of the statistical methods

The 2 groups will be defined according to the number of consultations honored each year over a 2-year period. Patients who have attended at least an average of 2 consultations per year for 2 years, i.e. a minimum of 4 sessions over 2 years, will be included in the experimental group Patients who do not reach this number will be included in the control group.

The categorical variables will be presented by their numbers and percentages, and compared by Fisher's exact tests or chi2. Quantitative variables will be presented by their median and interquartile range, or by their mean and standard deviation, and compared by t-tests or Wilcoxon tests, depending on their distribution

The rates of recurrence, hospitalization, pedicure follow-up and adapted footwear will be compared between the 2 groups by Fisher exact tests.

The time to recurrence in each group will be measured by the Kaplan-Meier estimator, and compared between the 2 groups by a log-rank test. If the conditions for application are met, the time to recurrence will be analyzed by a multivariate Cox regression model taking into account the characteristics of the patients (age, sex, length of diabetes, presence of arterial disease, neuropathy) as well as whether or not they were followed up in a "foot in remission" consultation, whether they had pedicures and whether they wore adapted shoes.

The results of the multivariate Cox regression study took into account the characteristics of the patients (age, sex, length of diabetes, presence of arterial disease, neuropathy) as well as whether or not they were followed up in a "foot in remission" consultation, whether or not they had received pedicure and whether or not they wore adapted shoes.

All tests will be performed in a two-sided manner, with a 1st species risk alpha fixed at 5%. The statistical analysis will be performed by [name] of the Clinical Research Unit of the CHSF, using the R software (R Core Team (2021). R: A language and environment for statistical computing. R Foundation for Statistical Computing, Vienna, Austria. [https://www.R-project.org/](http://www.R-project.org/))).

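### Calendar period is left out of both the 2-year group comparison and the Cox model, although groups are defined by visit counts in individual windows spread over 2017-2021 (minor, conditional confounding risk)

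*Protocol*

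**What the plan says.** Under Study population, entry requires "Discharge from hospital from a foot wound between 2017 and 2019 with a 2 years post-healing follow-up". Under Duration of the research, the data span is given as "Period of time for which data is available : 2017-2021". Under Nature of data collected, the exposure is recorded as "Number of follow-up visits honored over a two-year period from the time of healing", so each patient has an individual window.

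Under Conduct of the research, "The 2 groups will be defined according to the number of consultations honored each year over a 2-year period". Description of the statistical methods repeats the rule and sets the threshold, "i.e. a minimum of 4 sessions over 2 years", adding that "Patients who do not reach this number will be included in the control group". The threshold is the same whatever the calendar date, and the reason for a missed visit plays no part.

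For the analysis, "The rates of recurrence, hospitalization, pedicure follow-up and adapted footwear will be compared between the 2 groups by Fisher exact tests"; this is unadjusted and includes the primary outcome. The Cox model for time to recurrence is described as "taking into account the characteristics of the patients (age, sex, length of diabetes, presence of arterial disease, neuropathy"), together with specific follow-up, pedicure care and footwear. Neither healing date nor calendar period appears in the group rule, the Fisher comparison or the covariate list.

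**The concern.** Exposure here is a count of attended visits, and the chance of reaching four depends on how available visits were during the patient's window. Windows starting in 2017 close by the end of 2019. Windows starting late in 2019 lie almost wholly in 2020-2021.

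If visits became harder or easier to attend over that span, the later-healed patients would be distributed differently between the groups. If the occurrence or recording of recurrence also changed, calendar period would be a common cause of group and outcome. Part of any difference, or of its absence, would then reflect when patients healed rather than how they were followed. The planned unadjusted test cannot separate the two, and the Cox model as listed has no term that would.

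**Working it through.** The protocol gives no figure on this point to reproduce. The 158 patients are a count, and the sample size section disclaims any calculation.

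**Inputs from the protocol.** Discharge 2017-2019; 2 years from healing; cut-off of 4 visits; 158 patients; 1-year recurrence of 25% with specific and 40% with conventional follow-up (Expected outcomes section).

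**Assumed inputs.** Healing dates even over 2017-2019; 2.2 visits per year on average; constant recurrence hazard; the changes f and g defined in step 3; and mid-March 2020 as an alternative date of change. None of these is in the documents.

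**1. Spread of windows.** One third of patients (healed in 2017) have no follow-up in 2020-2021. For the other two thirds the time there runs from 0 to 2 years, mean 1 year, so the average share of follow-up in 2020-2021 is (2/3 × 1)/2 = 33%. Taking mid-March 2020 instead, windows overlap if healing falls from 17 March 2018 to 31 December 2019: 655/1095 days = 0.598. About 60% overlap and 40% do not.

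**2. Mechanism by hand, with no effect of follow-up.** Let 60% reach 4 visits in non-overlapping windows and 40% in overlapping ones, with recorded recurrence 45% and 35% respectively, the same in both groups within each period.
- Experimental: (0.4×0.6×45% + 0.6×0.4×35%)/(0.24 + 0.24) = 40.0%.
- Control: (0.4×0.4×45% + 0.6×0.6×35%)/(0.16 + 0.36) = 38.1%.
- Spurious difference: +1.9 points, against follow-up.
- If recurrence is 45% in both periods, both groups show 45%: no difference.
- If attendance is 60% in both periods, both groups show 0.4×45% + 0.6×35% = 39%: no difference.

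So both attendance and recorded recurrence must change.

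**3. Simulation, no effect of follow-up.** Let t be the years of a patient's window falling in 2020-2021. Visits are Poisson with mean 2.2 × [(2 − t) + f·t]. Two-year recurrence is 1 − 0.6^[(2 − t) + g·t], which takes 40% at 1 year as its base. Here f multiplies the visit rate and g the recorded recurrence hazard from 2020.

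| f | g | Experimental | Control | Difference (points) | Odds ratio |
|---|---|---|---|---|---|
| 0.6 | 1.0 | 63.9% | 63.9% | 0.0 | 1.00 |
| 1.0 | 0.6 | 58.3% | 58.3% | about 0 | 1.00 |
| 0.8 | 1.5 | 68.7% | 69.9% | -1.2 | 0.94 |
| 0.6 | 1.5 | 68.0% | 70.4% | -2.4 | 0.89 |
| 0.4 | 1.5 | 67.3% | 70.9% | -3.6 | 0.85 |
| 0.6 | 0.6 | 59.7% | 56.8% | +2.8 | 1.12 |
| 0.4 | 0.6 | 60.6% | 56.4% | +4.3 | 1.19 |

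Differences are taken before rounding. A rise in recurrence favours the experimental group; a fall favours the control group. With 158 patients the false-positive rate goes from 5% to about 8% at most.

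**4. Does the remedy work?** Stratifying on narrow bands of healing date (one eighth of a year) brings every scenario to within 0.2 points of zero. Evaluating the step 3 formulas over even healing dates and pooling strata with weights ab/(a+b), where a and b are the group sizes, the worst case of +4.3 falls to about +0.6 with three strata by year of healing. With only two strata (closed before versus overlapping mid-March 2020) it falls to about +1.8, because overlapping windows differ widely in how much they overlap.

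**The case against.** The strongest objection is that the premise lies outside the documents. No section mentions restricted access, missed visits or incomplete recording in 2020-2021. That stands: the point can only be conditional. What the documents do establish is that windows are spread over five calendar years and that the analysis ignores where they fall.

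Four stronger readings are tempting and are not supported.
- *Restricted access did shift the groups.* The protocol is dated April 2021 but reports no such change.
- *Fewer visits alone bias the result.* They reclassify patients but create no difference under no effect (steps 2 and 3).
- *The bias manufactures a benefit.* Fewer visits with less recorded recurrence work against follow-up. A spurious benefit needs fewer visits with more recurrence, and the documents point to neither.
- *The bias could be large*, for instance if recorded recurrence fell from 50% to 30% in every overlapping window. With even healing dates this cannot happen at constant hazard. Overlapping windows have on average (655/2)/730 = 45% of their time after mid-March 2020. Even if nothing were recorded after that date, their average recurrence would still be 1 − 0.5 × (e^x − 1)/x = 30.7%, with x = (ln 2 / 2) × 655/365.25 = 0.62.

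The simulation may itself overstate the late events. Constant hazard at 40% per year implies 1 − 0.6³ = 78% at 3 years, whereas the résumé gives 60%. That suggests more early recurrence, while the overlap is always the end of a window.

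It can also be said that a period term belongs in a statistical analysis plan, which is not at hand. This stands in part: such a plan could add it. But the protocol itself names the test and the covariates, so the omission is in what it fixes, not only in what it defers.

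**Conclusion.** The point holds in a limited form. The text confirms individual windows across 2017-2021, one visit threshold for all, an unadjusted 2-year comparison and a Cox covariate list without calendar period. Confounding follows only if attendance and recorded recurrence both changed over these years, which is an assumption.

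Under the ranges tried (f from 0.4 to 1, g from 0.6 to 1.5, even healing dates), the spurious difference is about -3.6 to +4.3 points at 2 years. The protocol's expected contrast is 40% − 25% = 15 points, at 1 year. The direction cannot be stated in advance. This is a minor, secondary threat, worth addressing because protection is nearly free.

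**What to change.** In Description of the statistical methods:
- Record the healing date as a named variable and stratify or adjust the 2-year comparison by year of healing, for example with a Mantel-Haenszel risk difference and test alongside the Fisher result.
- Add year of healing to the Cox model, as a stratum or a covariate.
- Add a sensitivity analysis limited to windows closed before March 2020. That date is itself an assumption; if the centre's own records show another date of change, use it and state it in advance.

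A two-level split, before versus overlapping March 2020, is an acceptable simpler choice but leaves more residual confounding than year of healing (step 4).

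Cost: no new data, since the healing date already starts the 2-year clock, and one extra factor in each analysis. The restricted analysis keeps about 40% of patients if healing is evenly spread, roughly 0.40 × 158 = 63. It will be imprecise and should be read for consistency with the main result rather than for significance.

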###### Number of centers

Monocentric research — cf. addenda n°1

###### Subjects identification

In this research, subjects will be identified as follows :

n° centre (3 numéric positions) — order of selection of the person in the center (4 numéric positions ) - initial name - initial first name '

I_0_I_1_I - I_0_I_0_I_0_I_1_I - I_N_I_P_I

This reference is unique and will be kept for the duration of the research.

###### Sources of personnal data

Data will be collected from patients' medical records.

###### Study population

- - 1. **Inclusion criteria**
- Patient with a type 1 or 2 follow-up at the Centre Hospitalier Sud-FranciIien (CHSF),
- Discharge from hospital from a foot wound between 2017 and 2019 with a 2 years post-healing follow-up
- Age greater than or equal to 18 years,
- People not deprived of liberty,
- Subject informed of the study and did not object.

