###### Methods of informing the population concerned

Each patient will be informed by an information note that he/she will receive at home. In case of no response from the patient or no refusal within 15 days after the letter is sent, the patient will be considered to be in favor of inclusion in the study..

12/14

Protocole Pied-REM ». version 1.0 du 19/04/2021

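### The inclusion criterion appears to require a completed 2-year follow-up after healing, which selects patients on events after time zero and biases the comparison by an unknown amount in an unknown direction.

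*Protocol*

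**What the plan says.** Under Study population (and in the Resume table), one inclusion criterion is "Discharge from hospital from a foot wound between 2017 and 2019 with a 2 years post-healing follow-up". Another is "Subject informed of the study and did not object". Conduct of the research says that eligibility is checked in the patient record. It then sets the order of steps: "After sending the information form to the patients and respecting the no-objection period, the patients will be included in the study".

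Methods of informing the population concerned adds: "Each patient will be informed by an information note that he/she will receive at home". Silence counts as agreement: the rule applies "In case of no response from the patient or no refusal within 15 days after the letter is sent".

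Groups are formed from attendance over two years: "The 2 groups will be defined according to the number of consultations honored each year over a 2-year period". At least four visits puts a patient in the experimental group. For the rest, "Patients who do not reach this number will be included in the control group". The primary outcome is recurrence of a foot wound at 2 years.

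Nature of data collected starts the observation period at healing. It lists neither date of death nor date of last contact. Description of the statistical methods plans Fisher exact tests on the rates and also a survival analysis: "The time to recurrence in each group will be measured by the Kaplan-Meier estimator", with a log-rank test and, if its conditions are met, a Cox model.

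**The concern.** Time zero is healing. If the criterion means that two years of follow-up must be on record, whether a patient belongs to the cohort is known only 24 months later, after group and outcome have both been determined. Patients who die or drop out early are then not censored. They are never entered.

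This matters because having a full record can depend on both attendance and recurrence. Four or more honoured visits over two years largely guarantee such a record. A low attender needs some other contact to have one, and whether that contact is related to recurrence decides how far the control rate is distorted. Deaths disappear from both groups uncounted.

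The analysis cannot repair this, because the excluded patients' data are not collected. Nor does the design need the restriction: the planned Kaplan-Meier and Cox methods can use incomplete follow-up.

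**Working it through.** **No stated figure to reproduce.** The protocol gives no death rate, loss rate or retention rate, so the size can only be illustrated.

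**Which reading of the criterion?**
- *Completed follow-up:* eligibility is checked in the record, records are the only data source, no death or last-contact date is collected, and a Fisher test on 2-year recurrence needs a known status at 2 years.
- *Calendar only (24 months could have elapsed):* data run from 2017 to 2021. A patient discharged in late 2019 whose wound healed in 2020 would need data into 2022, so a calendar condition would have a purpose. Kaplan-Meier also fits incomplete follow-up.

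The first is the more natural reading, but the text does not exclude the second.

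**Assumed true 2-year control recurrence.** The protocol gives 60% at 3 years (Resume, scientific justification) and 40% at 1 year with conventional follow-up (Expected outcomes).
- Constant hazard from the 3-year figure: 1 − 0.4^(2/3) = 45.7%.
- Log-linear interpolation of the recurrence-free proportion between years 1 and 3: 1 − √(0.6 × 0.4) = 51.0%.

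**Selection formula.** With true risk p, and a share rR of control recurrers and rN of control non-recurrers having the required record:

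observed control risk = p·rR / (p·rR + (1 − p)·rN)

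The experimental group is taken as fully retained and the true effect as nil. All retention values are assumptions.

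| rR / rN | p = 45.7% | p = 51.0% |
|---|---|---|
| 0.9 / 0.9 | 45.7% (0) | 51.0% (0) |
| 0.9 / 0.8 | 48.6% (+2.9) | 53.9% (+2.9) |
| 0.9 / 0.7 | 52.0% (+6.3) | 57.2% (+6.2) |
| 0.9 / 0.6 | 55.8% (+10.1) | 61.0% (+10.0) |
| 0.8 / 0.9 | 42.8% (−2.9) | 48.1% (−2.9) |
| 0.7 / 0.9 | 39.6% (−6.1) | 44.7% (−6.3) |

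Example: 0.51 × 0.9 / (0.51 × 0.9 + 0.49 × 0.6) = 0.459 / 0.753 = 61.0%.

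**Visits caused by a recurrence.** A recurrence can generate visits and carry a patient over the four-visit line. Assume 40% would attend four or more visits anyway, p = 45.7% and control retention 0.9 / 0.7.
- If 10% of low-attending recurrers cross: experimental 0.2102 / 0.4274 = 49.2%; control 0.2221 / (0.2221 + 0.2281) = 49.3%. The +6.3 points have all but cancelled.
- If 20% cross: experimental 0.2376 / 0.4548 = 52.2%; control 0.1974 / (0.1974 + 0.2281) = 46.4%. The bias is now about −6 points.

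**Effect on the test.** In simulation (158 patients, no true effect, two-sided Fisher test at 5%, 4,000 runs), significant results favouring the experimental group rose from about 1–2% to about 9–10% under 0.9 / 0.7 retention with no crossing. With 20% crossing, about 10% of results were instead significant in favour of control.

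**Information rule.** Silence within 15 days is agreement, so a living patient who is out of touch stays in. A patient who died before the letter went out cannot be informed, even if the death came after the 24-month window. The protocol does not say how such patients are handled.

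**The case against.** The strongest reply is that the criterion merely describes the observation window. The control group has no minimum attendance, so patients who stopped coming are the people it is meant to contain. That reading is possible. It does not remove the point, because staff applying the sentence as written could exclude deaths and losses, and nothing in the protocol tells them not to.

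A reader might infer that the control group is enriched with patients who came back because they recurred, so that the design manufactures a benefit. The documents do not support this. Nothing in them says why low attenders have records, equal retention gives no bias, and recurrence-driven visits push the other way.

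A reader might also infer that the information rule drops patients lost to follow-up. It does not, because no reply counts as agreement.

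Nor should the illustrated bias be set against the protocol's expected 15-point difference (25% against 40%). Those are 1-year rates, and the bias is at 2 years.

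A fair warning concerns the remedy. Dropping the follow-up requirement while keeping the four-visit rule would place most early deaths and losses in control by construction. This objection stands and shapes the fix. It is also true that competing-risk detail may be left to a statistical analysis plan, but the eligibility rule and the list of collected data are fixed here.

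**Conclusion.** The point holds in a limited form. On its natural reading the criterion conditions entry on follow-up completed after time zero, within the window that also sets group and outcome. The information rule may add a requirement to be alive at mailing. The selection bias has unknown size and direction. Under the assumed recurrence of 46% to 51%, retention of 90% of control recurrers and 60% to 80% of control non-recurrers, and full retention of the experimental group, the observed control rate is about 3 to 10 points too high. Other equally admissible assumptions give zero or a negative bias. The wording and the data list should be settled before data collection, since the missing patients cannot be recovered in the analysis.

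**What to change.** 1. Reword the criterion so that eligibility is fixed at healing: every adult with diabetes discharged after a foot wound in 2017–2019 whose wound healed and for whom 24 calendar months could be observed by the data cut-off. Require no completed follow-up.
2. Add date of death and date of last documented foot status to Nature of data collected.
3. Follow each patient to first recurrence, death, last documented foot status or 24 months, whichever comes first. Censor losses and treat death as a competing event.
4. In this analysis, enter attendance as a time-dependent covariate or use a landmark, so that early deaths and losses are not assigned to control by construction. Keep the comparison in patients with complete follow-up as a sensitivity analysis.
5. Ask the ethics committee how records of deceased patients may be used. If they cannot be used, report exclusions by reason and visit level, and state that the results apply to survivors.

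The cost is some additional charts from the same database, two more dates per record and some censored follow-up.
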